#### Sample Size Calculations

Given the planned study design with two treatment conditions (real and sham tDCS), two time points (before and after the intervention) and three diagnostic groups (anxiety, depressive and conduct disorder), a repeated-measures analysis of variance (rmANOVA) with the following parameters was set up: α = 0.0167 (0.05 corrected for three groups), power 1 – β = 0.80, a moderate effect size of f = 0.25 (73). The FEEL-KJ [German version of the Questionnaire for the assessment of emotion regulation in children and adolescents; (74)] as it is used for assessment of the primary endpoint was reported to have a test-retest reliability of r = 0.62, a Chronbach alpha of α = 0.93 for the adaptive strategy subscale and a Chronbach alpha of α = 0.82 for the maladaptive strategies, whereas for the 15 different emotion specific subscales Chronbach alphas between α = 0.69 – α = 0.91 were reported (74). Non-sphericity is of no relevance for only two repeated measures. This, results in a required sample size of 36 per group and 108 subjects overall.

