#### Stratification and Randomization

In a first step, participants displaying T-values of the FEEL-KJ Total score outside the clinical norm (T-value <40 or >60 in accordance with the transdiagnostic inclusion criterion of substantial emotion dysregulation) and in addition fulfilling the primary diagnosis of either a depressive, anxiety or conduct disorder, will be included in the study. Secondary diagnosis, especially comorbid disorders related to another subgroup of the current trial (e.g., primary diagnosis: depression and secondary diagnosis: anxiety) will be recorded and taken into consideration for the analysis. Age and sex will serve as stratification variables allocating 12 participants of each clinical group to one age block (age block1: 13 + 14 years; age block 2: 15 + 16 years; age block 3: 17 + 18 years) with half of the participants per age block being female and the other half male.

In a second step, a block randomization is performed: 50% of the participants of each block of each subgroup will be randomly allocated to the real or sham tDCS group, respectively (18 of 36 for each of the three clinical groups, female: male = 1:1). This results in 54 subjects per experimental condition (balanced related to clinical groups, age and sex; see Figure 1).

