### Statistical Analysis

Regarding the primary endpoint, repeated-measures analysis of variance (rmANOVA) with Time (pre/post) and Treatment Condition (real stimulation/sham stimulation), as well as considering the three clinical subgroups will be conducted to investigate the interaction between times and groups on the dependent variable [FEEL-KJ raw scores (74)]. The sex and age of the participants will be used as blocking factor accounting for treatment variability between males and females and the three age groups, respectively. In the case of distributions not suitable for conventional testing and missing values, a generalized linear mixed model on the relationship between the stimulation condition and behavioral variables can be applied. Stimulation condition and time will be taken as the fixed-effect factors and the participant's ID as the random-effect factor. Parameters of the model will be fitted with the maximum-pseudolikelihood method, the appropriate distribution and link function according to the characteristics of the response data. A marginal ANOVA will follow to evaluate the fix-effect factors significance. The secondary endpoints, i.e., the indicators for aggression, depression, anxiety and quality of life, as well as cognitive and emotional functioning will be compared using the same approach. In order to identify the direction of effects, *post-hoc* tests will be employed.

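### The strata used for randomisation are not reliably carried into the test of change: the fallback mixed model omits them, and the repeated-measures ANOVA does not say that they are crossed with time

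*Protocol article*

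**What the plan says.** Under *Stratification and Randomization*, the Protocol article fills each diagnosis with 12 patients per age block, half of each sex, and then allocates within blocks: "50% of the participants of each block of each subgroup will be randomly allocated to the real or sham tDCS group". That makes 18 cells (3 diagnoses x 3 age blocks x 2 sexes) of 6 patients, split 3:3.

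Under *Statistical Analysis*, the primary test is the interaction of time (pre, post) and group on the FEEL-KJ raw score, in a repeated-measures ANOVA that also takes account of the three clinical subgroups. On the other two strata it says: "The sex and age of the participants will be used as blocking factor accounting for treatment variability between males and females", and the same for the three age groups. It does not say whether they enter as main effects or crossed with time.

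The same section allows a generalized linear mixed model where values are missing or distributions are unsuitable. It names the terms of that model: stimulation condition and time as fixed effects, participant ID as the random effect. Diagnosis, sex and age are not among them. Secondary endpoints follow the same approach.

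*Sample Size Calculations* sets the scale of the test: "α = 0.0167 (0.05 corrected for three groups", "power 1 – β = 0.80" and "a moderate effect size of f = 0.25".

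**The concern.** With two time points, the time x treatment test is a comparison of post-minus-pre differences between arms. A sex or age effect that is the same at both times subtracts out of each patient's difference. As a main effect it therefore cannot do what the article wants from it, which is to account for variability between the sexes and age groups in the response to treatment. Only terms crossed with time can do that.

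The allocation is balanced within cells, so differences in change between cells do not add to the error of the treatment estimate. If the model has no stratum-by-time terms, however, those differences stay in the residual. The standard error is then too large and the test rejects too rarely. The precision that stratified randomisation can give is lost without anyone having decided to give it up.

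There is a reason within the document to take this seriously for sex: males and females receive different electrode montages (*Electrode Placement and Current Strength*). The three diagnosis-specific comparisons, which belong to the primary hypothesis, have only 36 patients each and would gain most.

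**Working it through.** **1. The plan's own sample size.** Inputs from *Sample Size Calculations*: alpha = 0.0167, power 0.80, f = 0.25, m = 2 time points, two arms. The quoted reliability ("was reported to have a test-retest reliability of r = 0.62") is taken as the pre/post correlation.

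For the within-between interaction, lambda = f² × N × m / (1 − rho), on 1 and N − 2 degrees of freedom.

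- N = 36: lambda = 0.0625 × 36 × 2 / 0.38 = 11.84; power 0.816.
- N = 34: lambda = 0.0625 × 34 × 2 / 0.38 = 11.18; power 0.788.

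So 36 per diagnosis, and 3 × 36 = 108, reproduce the statement that the calculation "results in a required sample size of 36 per group and 108 subjects overall". The calculation is a two-arm test within one diagnosis. In standard deviations of change, the design effect is √(4 × 0.0625 × 2 / 0.38) = 1.147.

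**2. Main effects cancel.** Let Y(post) − Y(pre) = D for each patient. A term b × sex that is present at both times contributes b − b = 0 to D. In a simulated data set of 36 patients with sex and age effects, fitted by least squares:

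| Model | time x treatment estimate | t | residual df |
|---|---|---|---|
| time x treatment | 0.3186 | 1.3346 | 34 |
| plus sex and age main effects | 0.3186 | 1.3346 | 34 |
| plus time x sex and time x age | 0.3186 | 1.3594 | 31 |

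The estimate is the same in all three because allocation is balanced. Only the terms crossed with time change the standard error.

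**3. Size of the conservatism, by hand.** Let R² be the share of the variance of change explained by the strata. The article gives no figure, so R² is an assumption. Under balanced allocation the true variance of the treatment estimate is proportional to 1 − R², while the model without stratum-by-time terms estimates it as if R² were 0. The actual type I error is then roughly 2 × P(Z > z / √(1 − R²)). The two-sided critical value at 0.0167 is z = 2.393.

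- R² = 0.10: 2.393 / √0.90 = 2.523, giving 0.0116.
- R² = 0.20: 2.393 / √0.80 = 2.676, giving 0.0075.

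**4. The same by simulation.** One diagnosis, N = 36, six sex-by-age cells of 6 split 3:3, alpha 0.0167; 60,000 replicates for type I error and 20,000 for power at the design effect.

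| R² of sex and age (assumed) | Type I, no time x block terms | Type I, with terms | Power, no terms | Power, with terms |
|---|---|---|---|---|
| 0 | 0.016 | 0.016 | 0.82 | 0.81 |
| 0.05 | 0.014 | 0.017 | 0.82 | 0.84 |
| 0.10 | 0.012 | 0.017 | 0.83 | 0.86 |
| 0.20 | 0.008 | 0.018 | 0.84 | 0.90 |
| 0.30 | 0.004 | 0.017 | 0.85 | 0.94 |

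For all 108 patients, type I error without the terms falls in the same way (0.012 at 10%, 0.008 at 20%), but power at the design effect is about 0.9996 or higher with or without them.

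**5. Cost of the terms if they are not needed.** Within one diagnosis they use 1 (sex) + 2 (age block) = 3 degrees of freedom. Power at N = 36 goes from 0.816 on 34 residual df to 0.813 on 31, a loss of 0.3 points.

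**The case against.** The strongest reply is that the article never says the blocks are main effects only. A standard repeated-measures ANOVA crosses between-person factors with time, and the stated purpose (variability in treatment response between the sexes) points to interactions if to anything. Diagnosis also appears to be a model factor already. A reader might infer from the words on blocking that the primary ANOVA ignores the stratification and is too conservative. The document does not support that: under the crossed reading the strata are used and the test keeps its level. This part of the objection stands, so for the ANOVA the point is one of ambiguity.

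A second reply is that the loss needs sex or age to predict change in FEEL-KJ, and the article gives no figure for this. That also stands. With R² = 0 nothing is lost, and every loss shown above is conditional on an assumed share.

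A third reply is that an article may leave the exact crossing of factors to a fuller plan. For the ANOVA this is fair. It is weaker for the fallback model, where the article does list the terms and the list leaves out every stratification factor. Use of that model is optional, but missing values, one of its two triggers, are plausible with ten stimulation sessions and several assessment visits.

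**Conclusion.** The point holds in a limited form. As listed, the fallback mixed model drops diagnosis, sex and age block. The primary ANOVA is open to a reading in which sex and age do nothing for the time x treatment test. In both cases the test is valid and is neutral to conservative.

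Per diagnosis at alpha 0.0167, power forgone at the design effect is about 3 points if sex and age explain 10% of the variance of change (0.83 against 0.86) and about 6 points if they explain 20% (0.84 against 0.90). It is nil if they explain nothing. A reader might infer that the trial is underpowered or its sample size wrong. Neither follows: power without the terms stays at 0.82 to 0.85 over the range examined, the planned 36 per diagnosis and 108 overall stand, and type I error is not inflated. What is forgone is a possible gain.

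The figures assume complete pre/post pairs, a linear model, balanced 3:3 cells, additive sex and age effects on change, and the quoted reliability as the pre/post correlation. With missing values or a non-identity link the cancellation is not exact, so for the fallback model the figures are a guide to direction and rough size. The priority is modest.

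**What to change.** State the within-person part of the model as time x (treatment + diagnosis + sex + age block), in both the primary repeated-measures ANOVA and the fallback mixed model, and use the same terms for the secondary endpoints. In the diagnosis-specific tests, drop the diagnosis term. If the software already crosses between-person factors with time, say so, so that the terms are fixed in advance.

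The cost is one line of specification and 2 (diagnosis) + 1 (sex) + 2 (age block) = 5 degrees of freedom overall, or 3 within one diagnosis. No further data or patients are needed.

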#### Eye Tracking and Behavioral Measures

##### Frankfurter Test and Training for Recognizing Facial Affect II

In this computerized task, the subjects have to identify basic emotions presented on 50 black and white photos of the entire face (113). The used stimuli are based on Ekman's concept basic emotions [happiness, sadness, anger, disgust, fear, surprise and neutral; (114)] and the test includes measurements of reaction times and correct classification.

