##### Emotional Stroop Task

Here we adapt an emotional conflict task (implicit regulation), as prior used to detect the activation of medial pre-frontal regions during emotion regulation (115, 116). This paradigm is built as a variation of the STROOP task. Participants have to identify happy or fearful faces, and are instructed to ignore the overlaid words “fear” and “happy” (“ANGST” or “GLÜCK” in German) *via* button pressing. A trial-by-trial adaptation to emotional conflict brings up an emotional regulatory mechanism (116). Here, behavioral reactions (correct/incorrect classification, omission) will be recorded.

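### With participant ID as its only random effect, the fallback mixed model tests real versus sham too liberally for task outcomes analysed as single responses or fixed-dispersion counts

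*Protocol article*

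**What the plan says.** The first-line analysis in the Statistical Analysis section is a repeated-measures ANOVA, and the secondary endpoints follow the same approach. Where distributions are unsuitable or values are missing, a generalized linear mixed model may be used to relate stimulation condition to behavioural variables. Its structure is stated: "Stimulation condition and time will be taken as the fixed-effect factors and the participant's ID as the random-effect factor". Its fitting is stated too: "Parameters of the model will be fitted with the maximum-pseudolikelihood method, the appropriate distribution and link function according to the characteristics of the response data". The fixed effects are then tested by a marginal ANOVA. For these outcomes the article names no participant-by-time term, dispersion parameter or robust variance. It does not say whether the data are single responses or one score per visit.

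The Outcomes section lists counts of correct responses, commissions and omissions among the task indices, next to reaction times and eye-tracking measures. For the emotional Stroop, "Here, behavioral reactions (correct/incorrect classification, omission) will be recorded". In the FEFA II, "the subjects have to identify basic emotions presented on 50 black and white photos of the entire face". The fMRI section gives 96 stimuli for the n-back, 149 for the Stroop and 42 for the emotion recognition task, all for the scanner versions.

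**The concern.** For right/wrong or omission data, a distribution suited to the response is naturally binomial or Poisson. A participant intercept removes stable differences between participants. It leaves no variance for one adolescent improving more than another between visits. With dispersion fixed at 1, the residual variance is set by the mean and cannot absorb that variation either. The standard error of the real-versus-sham difference in change then reflects item noise alone.

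The null hypothesis of interest is that mean change does not differ between arms. The reference distribution actually used assumes, in addition, that every participant changes equally on the model scale. Ordinary individual variation in change therefore counts as evidence for stimulation, and more so the more stimuli a task has. Adding a condition-by-time term to the fixed effects does not cure this. At stake are false claims of improved emotion recognition, implicit regulation or working memory.

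**Working it through.** **Inputs from the article.** Sample Size Calculations: "α = 0.0167 (0.05 corrected for three groups), power 1 – β = 0.80, a moderate effect size of f = 0.25"; "test-retest reliability of r = 0.62"; "This, results in a required sample size of 36 per group and 108 subjects overall". Stratification and Randomization: "This results in 54 subjects per experimental condition". Responses per visit: 50 (FEFA II), and 42, 96 and 149 (fMRI versions).

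**The plan's own figure.** For the time-by-arm interaction within one diagnostic group, with two visits and two arms, λ = f² × N × 2/(1 − ρ) = 0.0625 × 36 × 2/0.38 = 11.84. At α = 0.0167 this gives power 0.816, and 35 would already reach 0.80. So 36 per group and 108 overall reproduce. The article states no type I error for the mixed model.

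**Analytic check.** Let n be responses per visit, p the accuracy and σ the SD of true change in logits. The ratio of true to model-assumed variance of the change is R = 1 + n·p(1 − p)·σ²/2. The rejection rate at nominal 5% is 2[1 − Φ(1.96/√R)]. If the variation is written as a participant-by-visit SD s, then σ = s√2 and R = 1 + n·p(1 − p)·s². With assumed p = 0.8 and s = 0.31 (σ = 0.44):

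- n = 50: R = 1 + 50 × 0.16 × 0.0961 = 1.77, giving 14%
- n = 96: R = 2.48, giving 21%
- n = 149: R = 3.29, giving 28%

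**Simulations.** Both used 54 per arm, no arm difference, 1000 runs per setting, a binomial random-intercept model fitted by pseudo-likelihood with dispersion fixed at 1, and a test of condition × time. Accuracies and SDs are assumptions.

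Baseline accuracy 80%, between-participant SD 0.6 logit:

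| Responses | σ = 0 | 0.28 | 0.44 | 0.71 |
|---|---|---|---|---|
| 50 | 4.5% | 9.3% | 13.5% | 22.6% |
| 96 | 4.5% | 12.3% | 21.1% | 36.4% |
| 149 | 4.1% | 16.2% | 27.9% | 46.8% |

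Baseline logit 1.0 (42 responses), 1.4 (50 and 96) or 2.0 (149), that is, accuracy about 73%, 80% or 88%:

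| Responses | σ = 0 | 0.3 | 0.5 | 0.7 |
|---|---|---|---|---|
| 42 | 5.2% | 8.5% | 14.4% | 24.1% |
| 50 | 4.4% | 7.0% | 16.1% | 23.5% |
| 96 | 4.5% | 12.4% | 26.6% | 38.2% |
| 149 | 4.5% | 15.8% | 27.6% | 38.3% |

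For 149 responses, the lower figure at the right (38.3% against 46.8%) fits the higher assumed accuracy, which makes p(1 − p) smaller. For σ from 0.3 to 0.7, the formula gives 10.0% to 28.0% for 50 items at 75% accuracy and 7.4% to 17.6% at 90%. For 149 responses at σ = 0.7 it gives 48.4% and 34.4%.

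**Single-trial reaction times.** Here R = 1 + n·k²/2, with k the SD of true change over the SD of a single trial. For k = 0.1, 0.2 and 0.3 (assumed), the rate is 7.5%, 14.8% and 24.9% with 42 trials, and 13.8%, 32.6% and 48.0% with 149.

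**What removes the inflation.** Comparing each participant's change between arms rejected in 3.7% to 6.0% of runs over all these binomial settings. A Gaussian random-intercept model with one score per visit rejected in 5.0%, 4.9% and 5.7% when the SD of change was 0, 0.7 and 1.5 residual SDs. Estimating the dispersion (96 responses, σ = 0.5, 200 runs) gave 7.0%, against 26.6% with it fixed. That run used one count per visit, so it does not speak to single responses.

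**The case against.** The strongest reply is that the article does not fix the configuration that fails. The mixed model is optional, the distribution is left to suit the data, and pseudo-likelihood fitting allows an estimated dispersion. Many listed indices, such as mean reaction time or fixation duration, can be one score per visit with an estimated residual variance, which keeps the nominal error. All of this stands, and it makes the point conditional.

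The size is also open to challenge. The reliability of 0.62 belongs to the FEEL-KJ questionnaire. The value s = 0.31 gives a correlation of 0.36/(0.36 + 0.096 + 0.125) = 0.62 at 50 items, but that is a borrowed anchor and says nothing about task accuracy. The 96 and 149 counts come from the scanner versions; the behavioural Stroop and n-back sections give no counts, and the n-back adapts its difficulty to performance. Of the counts used, only the FEFA's 50 comes from a behavioural section. This stands too.

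The argument that such detail belongs in an unseen analysis plan carries less weight. The article does state the random structure, and a participant intercept alone is its natural reading, even if the sentence does not expressly exclude a time slope.

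**Conclusion.** The point holds conditionally. If the fallback is applied to single responses, or to binomial or Poisson counts with dispersion fixed at 1, a true null is rejected in about 7% to 28% of trials for a 50-item task. For about 149 responses the rate can exceed 40%. This rests on an assumed SD of true change of about 0.3 to 0.7 logit and accuracies of about 75% to 90%. At an SD of zero there is no inflation. The simulations were binomial; a Poisson model with fixed dispersion shares the mechanism.

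A reader might infer that the plan's behavioural analyses in general reject a true null far above 5%, or that the primary result is compromised. The article supports neither. The FEEL-KJ, the questionnaires and other outcomes with one score per visit and an estimated residual variance keep about 5%, and for counts an estimated dispersion removes most of the excess. The affected task indices are secondary or exploratory, so this is a cheap improvement.

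**What to change.** In the Statistical Analysis section, state the unit of analysis for each task outcome. For response-level or count outcomes, replace the single random factor with a random intercept for participant plus a participant-by-visit random effect (a random slope for time), and test condition × time against that variance. Alternatively, reduce each task to one score per participant and visit, for example the empirical logit of the proportion correct, and analyse it with a Gaussian mixed model.

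The cost is a sentence or two in the text and one more term in the code, with no new data or participants. The downside is wider confidence intervals for these outcomes.

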### Hypotheses

#### Primary Hypothesis

We expect that the participants of the experimental group (in total i.e., transdiagnostic, as well as in each clinical subgroup) will significantly improve in emotion regulation after real tDCS, when compared to the control group (in total i.e., transdiagnostic, as well as in each clinical subgroup) after receiving sham stimulation.

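### The fallback mixed model names only condition and time as fixed effects: the condition-by-time interaction, diagnosis, sex and age block are not stated, and its trigger is left open

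*Protocol article*

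**What the plan says.** The Primary Hypothesis section expects that the experimental group "will significantly improve in emotion regulation after real tDCS, when compared to the control group", overall and within each clinical subgroup.

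The Statistical Analysis section gives two models in one paragraph.

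- **Repeated-measures ANOVA.** The factors are time (pre/post) and treatment condition, "as well as considering the three clinical subgroups will be conducted", and the purpose is "to investigate the interaction between times and groups on the dependent variable", the FEEL-KJ raw score. The next sentence adds: "The sex and age of the participants will be used as blocking factor".
- **Fallback.** The trigger is worded "In the case of distributions not suitable for conventional testing and missing values, a generalized linear mixed model". Both its scope and its optional status come from the remainder of that sentence: "on the relationship between the stimulation condition and behavioral variables can be applied". Its terms are then given: "Stimulation condition and time will be taken as the fixed-effect factors and the participant's ID as the random-effect factor". Distribution and link are chosen to suit the response data. The test is stated last: "A marginal ANOVA will follow to evaluate the fix-effect factors significance".

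The paragraph closes by applying the same approach to the secondary endpoints.

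**The concern.** The hypothesis is that the pre-to-post change is larger under real than under sham stimulation. When baseline is one of the two outcome values in the model, that is the condition-by-time interaction. The ANOVA sentence says so. The fallback goes into enough detail to list fixed effects, random effect, fitting method and test, yet it does not mention the interaction.

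An analyst who follows the fallback to the letter would fit two main effects and report their significance. That raises three problems:

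- The condition main effect is not the treatment effect, because it mixes the baseline difference, expected to be zero under randomisation, with the post-treatment difference.
- Without diagnosis, the subgroup part of the primary hypothesis cannot be addressed. Sex and age block, on which the Stratification and Randomization section balances the arms, are also missing from the listed terms.
- The choice between the two models has no threshold and is made once distributions and missingness are known.

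**Working it through.** **Inputs.** From Sample Size Calculations: f = 0.25, alpha = 0.0167, target power 0.80, test-retest reliability 0.62 (taken as the pre-post correlation ρ), 36 per diagnostic group and 108 overall. From Stratification and Randomization: 18 real and 18 sham per diagnosis, 54 per arm in total. There are m = 2 time points and k = 2 arms.

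**Step 1: reproduce the planned sample size.** For a condition-by-time (within-between) interaction:

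λ = f² × N × m / (1 − ρ), df1 = (k − 1)(m − 1), df2 = (N − k)(m − 1).

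At N = 36: λ = 0.0625 × 36 × 2 / 0.38 = 4.5 / 0.38 = 11.84, with df 1 and 34. Power at alpha 0.0167 is 0.816. The smallest N that reaches 0.80 is 35, or 36 with equal arms, and 3 × 36 = 108. The stated figures are therefore reproduced by the interaction test. A pure time effect has the same λ and also gives about 36, but it would not compare the arms. The condition main effect would need N = 139.

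**Step 2: what a literal main-effects model estimates.** Assume equal baselines and an effect δ at post only, in SD units. The cell means are 0 and 0 (sham pre, post) and 0 and δ (real pre, post). The arm means over time are 0 and δ/2, so the condition main effect is δ/2. The interaction contrast is δ. Each effect corresponds to f = δ/4, so f = 0.25 means δ = 1.0 SD.

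**Step 3: power of each term on the same complete data.** For the condition main effect, λ = f² × N × m / (1 + (m − 1)ρ), so the divisor is 1.62 rather than 0.38.

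| N | λ, interaction | Power | λ, condition main effect | Power |
|---|---|---|---|---|
| 36 (one diagnosis) | 4.5 / 0.38 = 11.84 | 0.816 | 4.5 / 1.62 = 2.78 | 0.213 |
| 108 (overall) | 13.5 / 0.38 = 35.53 | >0.99 | 13.5 / 1.62 = 8.33 | 0.675 |

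Simulation with 5,000 replicates agrees: 0.81 against 0.21 at 18 per arm, and >0.99 against 0.67 at 54 per arm. The mean estimated condition effect was 0.50 SD for a true post difference of 1.0 SD.

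**Step 4: a smaller effect.** If the post difference were 0.5 SD (an assumption, half the planning value), simulated power at alpha 0.0167 with 54 per arm is 0.71 for the interaction and 0.16 for the condition main effect. At alpha 0.05 it is 0.84 against 0.30. The halving of the estimate does not depend on the effect size; the loss of power does.

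**Step 5: could the fallback come into play?** The article gives no dropout rate. If each of 108 participants independently had a 2% or 5% chance of a missing post score (assumed), the chance of at least one missing value would be 1 − 0.98^108 = 89% or 1 − 0.95^108 = 99.6%. Some missing data would be likely, though this does not show that the switch would be made.

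**The case against.** The other side has several good points.

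- **The switch is permissive.** A reader might infer that any missing value triggers the fallback. The text only says that the model can be applied, and it joins distribution problems and missing values with *and*. Nor do the documents show that the fallback is the analysis likely to be run.
- **The interaction is unnamed, not excluded.** The sentence lists factors and nowhere limits the model to main effects. The ANOVA is also introduced by its factors, with its aim given separately, and that aim may be meant to carry over. The sex and age sentence stands alone and could be meant for both models.
- **The scope is unclear.** The fallback is described for behavioural variables, and elsewhere the article separates behavioural tasks from questionnaires such as the FEEL-KJ. Still, the sentence sits within the primary-endpoint paragraph.
- **Most power lost overall** would be too strong a reading. At the planning values, the full-sample loss is from more than 99% to 68%. The 84% to 30% contrast uses an alpha and an effect size that are not the trial's.
- **False-positive inflation** is not quantified. Under the Blinding section, analysts of the main hypotheses do not know group assignment, which limits selective model choice without removing it.
- **An article may leave detail to the full plan.** That would cover silence. Here the article states the terms and the test, and those stated do not match the hypothesis.

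These points reduce the claim but do not remove it. The test of a primary hypothesis should not depend on readers inferring its key term.

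**Conclusion.** The point holds as a specification fault. The fallback names condition and time only and tests those factors. It does not name condition by time and does not carry over diagnosis, sex or age block. Its use is discretionary, with an ambiguous trigger.

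If it were followed literally, it would not test the primary hypothesis. Its condition effect would be half the post-treatment difference, and power would be as tabulated above: about 21% rather than 82% per diagnostic group, and 68% rather than more than 99% overall. These figures rest on equal baselines, a post-only effect of 1.0 SD, complete data, and the reported reliability of 0.62 serving as the pre-post correlation. They describe the literal reading, which the text permits but does not require. Since the secondary endpoints use the same approach, the ambiguity extends to them.

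**What to change.** Prespecify one mixed model for the FEEL-KJ, using all randomised participants with any FEEL-KJ data and applied whatever the missingness. Its terms should be:

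- condition, time and condition by time;
- diagnostic group and its interactions with condition and time, including the three-way term, so that the subgroup hypotheses can be tested;
- sex and age block;
- a random intercept for participant.

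Name condition by time as the tested term and report its estimate with a confidence interval. Keep alternative distributions or links as sensitivity analyses.

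If the sponsor prefers to retain the ANOVA as the main analysis, the minimum is to add these terms to the stated fallback, say whether it covers the FEEL-KJ, state whether distribution problems and missing values must both occur or either suffices, and set the threshold before unblinding.

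The cost is wording in the protocol or analysis plan. No further data are needed and the sample size stays at 108.
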